#### Frequency of analyses

The formal evaluation of the treatment effects will take place after full recruitment and follow-up. During the course of the trial, the trial statistician, masked to treatment allocation, will carry out periodic quality checks of data and a preliminary analysis of efficacy. The interim data analysis will provide additional means for quality assurance of the project without compromising the validity or integrity. The trial will be conducted and reported as per the recommendations of the CONSORT statement for RCTs.

#### Subgroup analyses

Subgroup analysis will be carried out with respect to age, duration of illness, number of previous episodes, gender and self-reported biological sex by adding a treatment with covariate interaction into the primary analysis model.

#### Cost–utility analysis

A cost–utility analysis from healthcare system and societal perspectives will be conducted to establish the cost-effectiveness of CaPE compared with TAU. The treatment groups will be compared with each other at baseline and then at subsequent follow-ups at 3, 6 and 12 months. EuroQol-5D data will be collected at these time points to measure patient quality of life; quality adjusted life-year (QALY) gains between groups will then be estimated and compared at baseline and at the end of the 12-month period. The costs of delivering CaPE and TAU will be collected and will include costs of staff time, including that of therapists and their training to deliver the intervention, resources and equipment used, and any remuneration given to patients for their time. Data on the direct and indirect costs to patients will be collected using a bespoke questionnaire and will include any additional equipment/aids paid out-of-pocket by patients for the sessions as well as time taken off work by the patient and the carer (if any) to attend sessions. Additional data regarding health service use and direct costs to the healthcare system will also be obtained using the Client Service Receipt Inventory, completed by both treatment groups at 3, 6 and 12 months. We will use standard published sources for unit costs where available and supplement this with local sources to convert resource use into monetary values. Costs will be adjusted for inflation to 2025 Pakistani rupees using appropriate inflators. To estimate the cost-effectiveness of CaPE, an incremental cost-effectiveness ratio will be calculated, defined as the difference in costs divided by the difference in QALYs between the treatment groups. Standard procedures will be followed for imputation of missing values as well as for analysis of uncertainty and non-normal distributions. Further statistical analysis of costs will be performed to test for statistical significance of results, and bootstrapping will be performed to estimate variability in key parameters. The robustness of each treatment will be shown through 95% confidence intervals around the cost-effectiveness ratio, with sensitivity analyses.

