### Study procedures

We have seven major recruitment centres, each with multiple out-patient psychiatric units. There are five recruitment sites in Karachi, three in Lahore and one each in Multan, Rawalpindi, Peshawar, Hyderabad and Quetta. Psychiatrists will identify potential participants and offer them information about the study. Those who agree will be contacted by the research team, pre-screened and provided detailed information about the study, including procedures protecting privacy and confidentiality. Potential participants will have a chance to ask questions prior to providing informed written consent. Participants will then undergo a screening assessment based on the eligibility criteria outlined in Appendix 1, followed by the baseline assessment. After that, an independent statistician will check the record of baseline measures and will randomise the participant to one of the two arms of the study. The participant will be contacted by the study coordinator at their recruitment centre within 1 week of randomisation to inform them about treatment allocation. The time and date of sessions will be set based on the participant's preference. Participants randomised to the intervention arm will be offered 12 weekly individual sessions. Each session will last for 60 min. All sessions will be delivered by a trained therapist, who will receive 2 months of training from senior therapists before starting the intervention. Assessments will be carried out at baseline and at 3, 6 and 12 months. The assessment scales will be administered in person and/or via secure videoconferencing software (an alternative to in-person assessment to allow for COVID-19 or travel restrictions) by trained research analysts masked to treatment allocation.

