#### Randomisation and masking

Participants will be randomised using a block randomisation technique in a 1:1 allocation to CaPE or TAU. Randomisation will be computer generated and use a random permuted block method with variable block sizes. The sample will be stratified by site, bipolar type (I or II) and self-reported biological sex, given the potential differences in recurrence rates in these groups. In line with best practice in RCTs, we have not included further stratification variables.^38^ We will assess other potential prognostic characteristics (age, duration of illness, number of previous episodes, gender) in our *a priori* subgroup analyses.

This will be an assessor-masked RCT. Owing to the nature of the interventions, clinicians in participating centres and the participants themselves cannot be masked to treatment allocation. Before assessments, participants will be asked not to reveal any information about treatment to assessors. To avoid unmasking, outcome assessors will be located separately from treatment providers, and we will assign new outcome assessors in cases of unintentional unmasking. Statistical analysis will be partially masked (knowing treatment groups, but not what each group is). The intention-to-treat analysis plan will help reduce the effect of attrition bias. Finally, registration on Clinicaltrials.gov and publication of results regardless of the outcome will both minimise reporting bias.

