### Sample size

From preliminary evidence collected during the pilot RCT,^24^ we estimated the mean time to recurrence as 10 weeks in the TAU group and 45 weeks in the CaPE group. This resulted in a hazard ratio of 4.51. For the purposes of the current study, we assumed a more conservative mean time to recurrence of 21.4 weeks for the TAU group. For a sample size of 240 (120 in each group), we would have more than sufficient power (0.91) to detect a low hazard ratio of 1.60, which approximately corresponds to a mean relapse time of approximately 34.2 weeks in the CaPE group, a difference that would be of clinical importance. The minimum detectable hazard ratio to attain 0.80 power is 1.49. To allow for a possible 20% attrition rate, we aim to recruit 300 participants in total. For within-subgroup analysis, the minimum detectable hazard ratio is 1.67 for larger groups (e.g. males, ~60% of the sample based on pilot-trial data) and 1.88 for smaller groups (e.g. females, ~40% of the sample based on pilot-trial data). For subgroups defined by medium cut-off points, the minimum detectable hazard ratio is 1.75. For the current design, we could only detect between-group differences in treatment effects with adequate power (0.80) when there are drastic group differences, for example a hazard ratio of 1.75 in one group and 3.5 in another. As the effectiveness of CaPE is not yet established, it is premature to further increase our sample size to power subgroup analyses. Nevertheless, preliminary subgroup analysis will inform power calculations for future studies.

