### Statistical analysis

The intention-to-treat principle will be used, with participants analysed according to their allocated group. Our primary outcome is time to recurrence observed within 12 months. The treatment effect will be evaluated using the Cox proportional-hazards model with treatment assignment as the primary predictor. Baseline measures of key clinical characteristics (duration of illness, number of previous episodes) and demographics (age, gender, self-reported biological sex) will be controlled in the model. The treatment effect will be illustrated by the estimated hazard ratio to relapse between the two groups. In addition, parametric survival analysis models^38^ will be employed when appropriate. In the widely used Weibull distribution case (for example), the parametric analysis will use a log-linear model on the scale parameter with treatment assignment as the primary predictor while controlling for the set of covariates described above. The regression coefficient on treatment assignment can be interpreted as the log hazard ratio between the two treatment conditions in terms of relapse. This will help estimate the mean time to recurrence for the two groups. As this is a multicentre trial, dependencies for participants from the same centre will be accounted for by including centre as a random effect.^25^ We will investigate levels of missing data, assumptions (e.g. missing at random) and predictors of missingness. Missingness will be addressed using multiple imputations, capitalising on fitting mixed models with maximum likelihood and appropriate sensitivity analyses.^39^ We will also conduct an exploratory mediation analysis to investigate the role of treatment adherence and bipolar disorder type (I or II) on 12-month outcomes. Statistical inference will be conducted using two-tailed tests with 0.05 as the level of significance and 95% confidence intervals with secondary outcomes adjusted for multiple comparisons as necessary. We will use the most appropriate analytic and graphical features of SPSS, STATA and R as relevant.

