### Assessment schedule

**Table d64e765:**

Instrument	Baseline	Month 3	Month 6	Month 12
Demographic questionnaire	✓			
SCID Longitudinal Interval Follow-up Evaluation (LIFE)^29^	✓	✓	✓	✓
Young Mania Rating Scale (YMRS)^30^	✓	✓	✓	✓
17-item Hamilton Rating Scale for Depression (HRSD-17)^31^	✓	✓	✓	✓
EuroQol-5D (EQ- 5D)^32^	✓	✓	✓	✓
Bipolar Recovery Questionnaire (BRQ)^33^	✓	✓	✓	✓
4-item Morisky Medication Adherence Scale (MMAS-4)^34^	✓	✓	✓	✓
Bipolar Knowledge and Attitudes Questionnaire (BKAQ)^33^	✓	✓	✓	✓
Client Service Receipt Inventory (CSRI)^35^	✓	✓	✓	✓
Childhood Trauma Questionnaire (CTQ)^36^	✓	✓	✓	✓
Illness Perception Questionnaire-Revised^37^	✓	✓	✓	✓

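### The cost section lists the service-use inventory at months 3, 6 and 12, but the assessment schedule also has it at baseline; reconcile the two and use the baseline cost as a covariate

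*Protocol article*

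**What the plan says.** All places are in the protocol article.

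- **Cost–utility analysis, service-use data:** the form is the "Client Service Receipt Inventory, completed by both treatment groups at 3, 6 and 12 months". Baseline is not named.
- **Appendix 3, Assessment schedule:** the row "Client Service Receipt Inventory (CSRI)^35" carries a tick in all four columns: baseline, month 3, month 6 and month 12.
- **Study procedures:** "Assessments will be carried out at baseline and at 3, 6 and 12 months".
- **Cost–utility analysis, opening:** "The treatment groups will be compared with each other at baseline and then at subsequent follow-ups at 3, 6 and 12 months". The next sentence uses these time points for the EuroQol-5D.
- **Cost–utility analysis, estimator:** the incremental cost-effectiveness ratio is "defined as the difference in costs divided by the difference in QALYs between the treatment groups". Bootstrapping and sensitivity analyses are planned. No baseline-cost covariate is named.

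**The concern.** One instrument has two stated sets of time points. The cost section says when the form is completed, not merely which completions enter the 12-month total. Staff working from that section could therefore leave out the baseline form, while staff working from Appendix 3 would collect it.

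This matters because service use before randomisation cannot be reliably reconstructed at month 3 or later. If it is missed, or collected at some sites only, no later analysis plan can adjust the cost comparison for it properly. Costs of care are usually skewed and vary between patients before treatment starts. A baseline measure is the natural covariate for reducing the noise in the cost difference, and the schedule already provides for it. At stake is the precision of a secondary economic analysis, which the Study objectives make conditional on the trial confirming effectiveness.

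**Working it through.** **1. The passages side by side**

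| Place | Baseline | Month 3 | Month 6 | Month 12 |
|---|---|---|---|---|
| Cost–utility analysis, inventory sentence | not named | yes | yes | yes |
| Appendix 3, inventory row | yes | yes | yes | yes |
| Study procedures, assessments in general | yes | yes | yes | yes |

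The cost-section sentence is the odd one out.

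**2. The plan's own figures (context only)**

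The article gives no standard deviation, precision or power for costs. Its figures concern the primary outcome: "For a sample size of 240 (120 in each group), we would have more than sufficient power (0.91) to detect a low hazard ratio of", the target value being 1.60, with mean times to recurrence of 21.4 and 34.2 weeks.

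- Expected events, assuming exponential times and 52 weeks of follow-up: 120 × [(1 − exp(−52/21.4)) + (1 − exp(−52/34.2))] = 120 × (0.912 + 0.781) ≈ 203.
- Power by Schoenfeld's formula, two-sided 0.05, 1:1: Φ(√203 × ln 1.60 / 2 − 1.96) ≈ 0.918, close to the stated 0.91.
- Recruitment: 240 / (1 − 0.20) = 300, as stated.

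These figures reproduce, and nothing in this point changes them.

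**3. What baseline adjustment would gain**

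In a randomised comparison, adjusting a mean difference for a baseline covariate multiplies its variance by about 1 − r² and its standard error by √(1 − r²). Here r is the correlation between baseline and 12-month cost. **Every value of r below is an assumption.**

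| r (raw costs) | Variance ratio 1 − r² | Variance reduction | Confidence interval narrower by |
|---|---|---|---|
| 0.1 | 0.99 | 1% | 0.5% |
| 0.3 | 0.91 | 9% | 4.6% |
| 0.5 | 0.75 | 25% | 13.4% |
| 0.6 | 0.64 | 36% | 20.0% |

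A simulation with 120 per arm and lognormal costs (log-scale SD 1) agrees approximately. It gives variance ratios of about 0.90, 0.73 and 0.60 at raw-scale r of 0.3, 0.5 and 0.6.

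**4. Two reasons the gain may be smaller**

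- *Scale of the correlation.* For lognormal costs with log-SD 1, a log-scale correlation ρ gives a raw-scale r = (exp(ρ) − 1)/(e − 1). At ρ = 0.5 this is 0.649/1.718 = 0.378, so 1 − r² = 0.857, a reduction of 14% instead of 25%. Simulation at ρ = 0.3, 0.5 and 0.6 gives reductions of about 5%, 16% and 26%.
- *Other cost components.* The cost total also includes delivery, training, out-of-pocket and time-off-work costs. Suppose, for illustration, that half the between-participant variance in total cost comes from components unrelated to baseline service use. Then r² halves, and the 25% reduction at r = 0.5 falls to 12.5%.

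**The case against.** **The cost-section sentence can be read benignly.** It may simply name the follow-up visits at which trial-period costs are collected. It does not say that the form is used at those visits alone, and both Appendix 3 and Study procedures point to a baseline form. This stands in part. A reader might infer that the trial will have no baseline cost at all, and the documents do not support that, because the schedule provides for one. The conflict remains, since the sentence speaks of when the form is completed.

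**The section does not clearly contradict itself.** A reader might set its opening sentence, on comparing the groups at baseline, against the later inventory sentence. But the opening leads directly into the EuroQol-5D. If it covers costs as well, it supports a baseline inventory. This objection stands.

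**The ratio's definition does not exclude adjustment.** A reader might infer that the plan rules out using baseline cost. It does not: a regression-adjusted difference is still a difference in costs, and covariates are commonly left to a fuller analysis plan. This stands. Silence on the covariate is not an error, and the regression is offered as an improvement.

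**Nothing is biased.** With "1:1 allocation to CaPE or TAU", the unadjusted difference is unbiased in expectation, and a bootstrap interval already reflects chance imbalance. This stands in full.

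**The gain could be small.** Participants enter euthymic, in remission and on medication stable for at least 3 months, while later costs may be driven by recurrence. Low correlations are therefore plausible. Translating one favourable assumed correlation into a sizeable equivalent gain in participants would go beyond what the documents support.

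**Conclusion.** The inconsistency is real and confined to one instrument: the cost section omits the baseline completion that Appendix 3 schedules and Study procedures supports. It should be reconciled, because a literal reading of the cost section would lose data that are hard to recover.

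The statistical consequence is minor. It concerns the precision of a secondary economic analysis, not bias, and leaves the primary outcome, the 0.05 level and the 300-participant target unchanged. The variance reduction from adjustment runs from about 1% to about 36% over assumed raw-scale correlations of 0.1 to 0.6. It is smaller if those correlations hold on the log scale, or if components unrelated to prior service use account for much of the cost variation. The documents do not allow a single figure.

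**What to change.** 1. In the Cost–utility analysis section, state that the inventory is completed at baseline, 3, 6 and 12 months, matching Appendix 3 and Study procedures.
2. Estimate incremental cost as the arm coefficient from a regression of 12-month cost on arm and baseline inventory cost, and refit that regression within each bootstrap sample.

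The cost is a few words and one covariate. No visit or form is added, because Appendix 3 already schedules the baseline completion. If any site has been working from the cost section alone, check whether its baseline forms exist.

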## Study objectives

To determine the effectiveness of the CaPE intervention compared with TAU in reducing the time to recurrence for people in Pakistan with bipolar I or II disorder currently in remission.To determine the effect of the CaPE intervention compared with TAU on clinical outcomes, quality of life and functioning.To estimate the cost-effectiveness of CaPE in a low-resource setting (i.e. Pakistan) (if the RCT confirms the effectiveness of CaPE in bipolar disorder).To explore participants’ and therapists’ perspectives on the perceived usefulness of the proposed intervention and to identify the barriers and facilitators of incorporating the intervention into routine clinical practice through process evaluation.

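### A 95% confidence interval around the cost-effectiveness ratio may not support a conclusion if the 12-month QALY gain is small; show joint uncertainty by net monetary benefit instead

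*Protocol article*

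**What the plan says.** The Cost–utility analysis section of the protocol article sets out an incremental cost-effectiveness ratio (ICER), "defined as the difference in costs divided by the difference in QALYs between the treatment groups". QALYs come from EQ-5D at baseline, 3, 6 and 12 months and are to be "estimated and compared at baseline and at the end of the 12-month period".

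On uncertainty the section makes three statements:
- On resampling: "bootstrapping will be performed to estimate variability in key parameters".
- On general method: "Standard procedures will be followed for imputation of missing values as well as for analysis of uncertainty and non-normal distributions".
- On what will be shown: "The robustness of each treatment will be shown through 95% confidence intervals around the cost-effectiveness ratio, with sensitivity analyses".

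Only the third names a display of joint uncertainty in costs and QALYs. Under Study objectives, the economic objective applies "if the RCT confirms the effectiveness of CaPE in bipolar disorder".

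**The concern.** The ICER is a ratio whose denominator is a difference in QALYs over one year. Two things go wrong when that difference is not separated from zero.

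First, the sign of the ratio loses its meaning. A cost difference of +100 with a QALY difference of −0.01 gives 100 / −0.01 = −10,000, so CaPE is dearer and worse. A cost difference of −100 with a QALY difference of +0.01 also gives −10,000, so CaPE is cheaper and better. Positive ratios have the same defect: better at a cost, or worse but cheaper.

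Second, the interval itself breaks down. A Fieller interval is unbounded whenever the 95% CI for the denominator includes zero. A percentile bootstrap interval has limits, but it orders replicates that stand for opposite decisions.

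At stake is the third objective, which asks whether CaPE is cost-effective. The trial could succeed on time to recurrence and still report an economic interval that cannot be read.

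**Working it through.** **1. The plan's own design figure.** The Sample size section states that "we assumed a more conservative mean time to recurrence of 21.4 weeks for the TAU group". With 120 analysable participants per arm it claims power of 0.91 at a hazard ratio of 1.60. Take exponential times, means of 21.4 and 21.4 × 1.60 = 34.24 weeks, censoring at 52 weeks and two-sided alpha of 0.05.
- Event probabilities: 1 − exp(−52/21.4) = 0.912 and 1 − exp(−52/34.24) = 0.781.
- Expected events: 120 × (0.912 + 0.781) = 203.
- Power: 0.918 (Schoenfeld) and 0.908 (Freedman), against 0.91 stated.

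The figure reproduces, so 120 analysable participants per arm is a fair basis for what follows. It concerns time to recurrence only. The article gives no QALY difference or SD and no cost figures.

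**2. Precision of the QALY difference (assumed SDs).** SE = SD × √(2/120), and the 95% CI excludes zero if the observed difference exceeds 1.96 × SE.

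| Assumed QALY SD | SE | Observed difference needed |
|---|---|---|
| 0.15 | 0.019 | 0.038 |
| 0.20 | 0.026 | 0.051 |
| 0.25 | 0.032 | 0.063 |

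**3. How often the QALY interval includes zero.** For a true gain d the probability is Φ(1.96 − d/SE) − Φ(−1.96 − d/SE).

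| True gain d | SD 0.15 | SD 0.20 | SD 0.25 |
|---|---|---|---|
| 0.02 | 82% | 88% | 91% |
| 0.03 | 66% | 79% | 85% |
| 0.05 | 27% | 51% | 66% |
| 0.08 | 2% | 13% | 30% |

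**4. What gain might the design effect imply?** Mean recurrence-free time within 52 weeks is m × (1 − exp(−52/m)), which is 19.5 weeks for m = 21.4 and 26.7 weeks for m = 34.24. The gain is 7.2 weeks, or 7.2/52 = 0.139 years. Suppose, as an illustration, that recurrence lowers utility by 0.1 to 0.3 for the rest of the year and that this is the only route to benefit. The QALY gain is then 0.139 × 0.1 = 0.014 to 0.139 × 0.3 = 0.042, which lies in the range where the table shows frequent trouble.

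**5. Behaviour of the intervals.** A simulation used 120 per arm, QALY SD 0.10 to 0.20, and, in arbitrary currency units, a mean cost difference of 100, cost SD of 300 and value per QALY of 5000. Coverage of a percentile bootstrap ICER interval was 0.80–0.92 at a true gain of 0.005 and 0.95–0.97 at 0.08 and above. The net monetary benefit interval stayed at 0.94–0.96 throughout. At gains of 0.02 to 0.05 the ICER interval covered at 0.95–0.98. The difficulty there is interpretation, not coverage.

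**The case against.** Several points against the concern are sound.

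- The plan does not name the percentile method. A Fieller interval, or replicates sorted by quadrant, would also fit the text. This stands, but neither restores a bounded, single-meaning interval when the QALY difference straddles zero.
- The general clause on standard procedures, the bootstrap and the sensitivity analyses leave room for a sound analysis. This stands, and it limits the consequence. It does not remove the sentence that says what will be shown.
- A value per QALY, the plane and the acceptability curve are details that an article may leave to a fuller plan. Their absence is not counted as an error here; they enter only as part of the remedy. Likewise, applying an incremental ratio to each treatment is loose wording, since the ratio is defined correctly just before.
- The economic objective depends on confirmed effectiveness. That makes gains near or below zero less likely, but the primary outcome is time to recurrence, so it does not ensure a clearly positive QALY difference.
- The pilot effect on quality of life was 0.88. Half of that, 0.44 SD, gives z = 0.44/√(2/120) = 3.4, and the QALY interval would include zero in only about 7% of trials. But the sponsor shrinks the pilot hazard ratio from 4.51 to 1.60. The same shrinkage on the log scale gives 0.88 × ln 1.60/ln 4.51 = 0.27 SD and about 43% of trials. Neither figure is a 12-month QALY effect, so this is illustrative both ways.

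A reader might infer that an interval for an ICER is meaningless in general, that the trial cannot tell whether CaPE is cost-effective, or that more data would not help. None of these follows. The interval behaves well once the gain is clearly positive, the planned data permit a better analysis, and the SE falls as the sample grows.

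**Conclusion.** The concern holds in a conditional form. The article fixes, as its only named display of joint cost–QALY uncertainty, a statistic that becomes unbounded or ambiguous when the QALY gain is small relative to its standard error. Nothing in the design guarantees a large enough gain. With 120 per arm and the assumed SDs, the risk runs from very likely at a gain of 0.02 to uncommon or moderate at 0.08.

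The SDs, gains, utility losses and cost inputs are all assumptions. The percentages describe how often the display would be hard to read; they do not measure wrong decisions on cost-effectiveness. This is a correctable reporting weakness in a secondary, conditional analysis. The primary outcome, sample size and data collection are unaffected.

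**What to change.** Replace the sentence on intervals around the ratio with text to this effect:

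- Report incremental costs and incremental QALYs, each with a 95% CI.
- Show joint uncertainty by incremental net monetary benefit, λ × QALY difference − cost difference, with a 95% CI over a stated range of values λ per QALY, using the bootstrap already planned. It is linear in both differences, so it has no pole and its sign has one meaning.
- Add the cost-effectiveness plane and the acceptability curve from the same replicates.
- Give the ICER as a point estimate, or state that CaPE is dominant or dominated. Attach an interval only when the QALY difference is clearly above zero.

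The cost is a change of wording and a few lines of code; no new data are needed. The one downside is that a range of values per QALY must be named. Naming it before allocation is revealed to the analyst avoids choosing it after seeing the result.
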